## Introduction

Over 12 000 patients are diagnosed with renal cancer in the UK every year,^1^ and the incidence is increasing by 2% annually.^2^ The number of kidney cancer cases has more than doubled since the 1970 s^1^. Small renal masses (SRMs; T1a lesions on Tumour Node Metastases (TNM)staging; ≤4 cm of largest axis) account for two-thirds of new diagnoses of kidney cancers,^3^ the majority of which are incidental findings on investigations for other ailments or non-specific symptoms.^4^

The natural history of the SRM seems largely indolent. It is known that some (up to 40%) do not grow, and the majority that do increase in size, tend to enlarge slowly, between 1 and 15 mm per year, and providing that they do not breach the 4 cm size threshold, pose a very low risk of metastasis (1%).^5 6^ Treatment options for SRMs include active surveillance, ablation (either cryoablation or radiofrequency ablation) or surgical excision (partial nephrectomy or radical nephrectomy).^7^

The mainstay in treatment of a SRM is partial nephrectomy.^7^ Partial nephrectomy is recommended whenever technically possible as it preserves kidney function while providing good long-term oncological control. However, it is complex surgery and is associated with a higher major complication rate (4.9%), compared with radical nephrectomy (1.3%).^8^ In most cases, partial nephrectomy is performed using the da Vinci surgical robot system which costs around £1.5–2 million to purchase. Robot-assisted partial nephrectomy is estimated to cost between £7000 and 11 900 per case once the purchase and maintenance of the robot are taken into account.^9^

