### Objectives and outcomes

The primary outcome is to test the feasibility of recruitment into a cohort embedded RCT in NEST of SRMs.

Secondary outcomes are as follows:Participant retention rate, measured annually by analysing the number of randomised participants retained and assessed with valid primary outcome data.Health-related quality of life, measured using the previously validated EuroQol -5domains-5levels (EQ-5D-5L) questionnaire prior to treatment and 3 months following treatmentTreatment complications, blood transfusion, intensive care unit admission, and renal replacement requirement rates, measured using clinical records during hospital admission, at 30 days postoperative and at 6 months.Length of hospital stay, time to return to pre-treatment activities and number of work days lost (in those who work), measured using clinical records and follow-up consultation (clinic or telephone) at 30 days and at 6 months.Costs incurred by health technologies, measured using NHS reference costs and also private and societal costs measured using patient completed questionnaire at time of treatment, at 30 days and at 6 months.

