### Sample size and recruitment

The aim of this study is to assess the feasibility of a large definitive trial comparing partial nephrectomy and percutaneous cryoablation in the treatment of SRM and to inform the design, sample size and outcome measures for a subsequent large multicentre prospective trial, so formal sample size calculations are inappropriate. We will aim to recruit 50 patients into the embedded randomised study, randomised equally between the two groups. This sample size will allow the assessment of whether the consent rate of 30% has been achieved with a 95% CI of ±11%. Sample sizes between 24 and 50 have been recommended to estimate the SD required for sample size calculation to allow design of a full trial.^20 21^ We anticipate being able to recruit at least 30% of eligible patients which equates to 25 patients annually, and a total recruitment time of 24 months.

Recruitment issues will be pre-empted and identified early by the qualitative researcher and their team, ensuring successful delivery of both the initial feasibility trial and full trial. This will include participant involvement in semistructured interviews and focus groups to explore views on the presentation of the study information, understanding of the trial process and reasons underlying decisions to accept or decline the trial. As part of the qualitative research effort, participants who volunteer to take part in structured interviews and focus groups will be asked to participate in additional visits. Trial management group members and clinician involvement will also take part in semistructured interviews to explore their perspectives on the study design, and their experiences with recruitment.

If interim analysis after 12 months of initiation of recruitment shows evidence of any of the following:consent rate of <30%,cryoablation results in more than a 50% increase in complications compared with partial nephrectomy at 90 days,the intervention results in more than a 50% increase in waiting time for treatment compared with the standard treatment group, then a detailed ‘plan of action’ will be formulated together with the qualitative research team to identify any areas in the recruitment/study pathway that can be improved. A detailed report will be presented to the Sponsor, Trial Steering Committee and the Data Monitoring Committee. If no remedial actions are deemed suitable, then the trial will be stopped.

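### The 12-month complication trigger is set at 90 days, when no complication assessment is scheduled, and at most about 9 patients per arm could then be evaluated

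*Protocol article*

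**What the plan says.** Under Sample size and recruitment, the protocol article sets a look 12 months after recruitment opens: "If interim analysis after 12 months of initiation of recruitment shows evidence of any of the following". Three conditions follow. The one at issue is that "cryoablation results in more than a 50% increase in complications compared with partial nephrectomy at 90 days". A condition that is met leads to a plan of action with the qualitative team and a report to the Sponsor, the Trial Steering Committee and the Data Monitoring Committee. After that, "If no remedial actions are deemed suitable, then the trial will be stopped".

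Under Objectives and outcomes, complications are to be "measured using clinical records during hospital admission, at 30 days postoperative and at 6 months". Table 1 has a Week 4 visit after the intervention and then Month 6, with no column between. The section on trial assessments places the first post-procedure review at 4 weeks and most later ones 6 to 12 months apart. The only measurement named at 3 months is the EQ-5D-5L questionnaire, which Table 1 does not show at that time.

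On numbers, the same section states: "We anticipate being able to recruit at least 30% of eligible patients which equates to 25 patients annually". The embedded trial is to randomise 50, split equally.

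**The concern.** The rule and the data collection name different times. A safety comparison at 90 days needs every patient's complications to be known up to day 90. The schedule guarantees this only from Month 6 onwards, when the 6-month review looks back over the interval. At the interim, many treated patients will have passed Week 4 but not reached Month 6.

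The second difficulty is size. A relative increase of 50% is judged on a handful of patients per arm, where one event more or fewer decides the result. The rule can set off remedial work, and possibly closure, in a study designed to overcome earlier recruitment failures. Its silence could also be taken as reassurance about safety that the data cannot give.

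**Working it through.** **Time points side by side**

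| Item | Times stated |
|---|---|
| Complication trigger (Sample size and recruitment) | 90 days |
| Complications as secondary outcome (Objectives and outcomes) | admission, 30 days, 6 months |
| Visits after intervention (Table 1) | Week 4, Month 6, then yearly columns |
| EQ-5D-5L (Objectives and outcomes) | before treatment, 3 months |
| Adverse events (Adverse events section) | recorded in notes, CRF and AE Log; log to Sponsor on request and every 2 months |

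No scheduled complication review falls between day 30 and Month 6.

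**Patients evaluable at the interim**

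Inputs: 25 patients a year and 1:1 allocation (protocol). Assumptions: even accrual and no wait between randomisation and treatment. Any wait lowers the numbers.

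- Randomised by 12 months: 25, or 12 to 13 per arm.
- With 90 days of follow-up (entered in the first 9 months): 25 × 9/12 = 18.75, about 9 per arm.
- With Month 6 reached: 25 × 6/12 = 12.5, about 6 per arm.

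So of about 9 per arm with 90 days elapsed, about 3 per arm have not yet had the review that would cover days 31 to 90.

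**How the ratio behaves**

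The article gives no operating characteristics for the trigger, so there is no planned figure to reproduce. Its only complication rate for partial nephrectomy is 4.9%, for major complications (Introduction). The trigger refers to complications without a grade, so control risks of 4.9%, 10% and 20% are used as an assumed range.

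Let X₁ and X₀ be the numbers of patients with a complication after cryoablation and partial nephrectomy, independent binomials with n = 9 each. The trigger probability is the sum of P(X₁ = i) × P(X₀ = j) over all pairs with i/9 > 1.5 × j/9. Pairs with j = 0 and i > 0 are counted as a trigger.

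| Control risk | Equal risks: fires | True doubling: fires | P(no control event) |
|---|---|---|---|
| 4.9% | 25.2% | 45.0% | 63.6% |
| 10% | 32.6% | 56.9% | 38.7% |
| 20% | 31.6% | 61.8% | 13.4% |

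The last column is (1 − risk)⁹; for example, 0.951⁹ = 0.636.

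**The zero-event convention**

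With no control event, a percentage increase is undefined and the article does not say how to treat it. At 4.9% with equal risks, the zero-control cases contribute 0.636 × (1 − 0.636) = 0.231 of the 0.252. With a true doubling (9.8%), they contribute 0.636 × (1 − 0.902⁹) = 0.636 × 0.605 = 0.385 of the 0.450. If they are not counted as triggers, a true doubling is flagged in only 0.450 − 0.385 = 0.065, or 6.5%, of studies.

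**Sensitivity to the number per arm**

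Ignoring the 90-day requirement and using 12 per arm, equal risks fire in 29% to 34% of studies and a true doubling in 50% to 65%, over the same risks. The picture does not depend on the exact count.

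**The case against.** The strongest reply is that a 90-day count can be derived without a 90-day visit. Complications come from clinical records, all adverse events are logged, permission for telephone contact is sought, and the EQ-5D-5L is due at 3 months. This stands in part. A reader might infer that there is no contact at all between Week 4 and Month 6, or that 90-day events cannot be known; the document supports neither. What remains is that none of these routes is a scheduled complication review, so events in days 31 to 90 may be missed at the interim.

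A second reply is that the rule says only that the analysis shows evidence of an increase, and that a criterion may sit in an analysis plan or committee charter not shown. That is fair. The probabilities above describe the ratio read at face value, which the wording permits but does not compel. A charter would not by itself remove the mismatch between the two sections.

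Third, the zero-event convention drives much of the false-trigger figure at the lowest risk. True, and it is shown above; the other convention lowers false triggers but leaves the rule nearly blind to a doubling.

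Fourth, a sensitive alarm may suit a feasibility study whose analyses are all called exploratory. A trigger leads first to a plan of action and reports, so automatic stopping should not be read into it.

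A reader might also extend the criticism to the other two triggers. The document does not support that:

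- For "consent rate of <30"%, the denominator can be read as about 25/0.30 = 83 eligible patients. The rule then fires in 98% of studies at a true 20% and 2% at a true 40%, and is near a coin toss only close to 30%.
- For waiting time, performance depends on a variability that the article does not give.

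Nor should the cryoablation group be shrunk by applying 30% acceptance again: the 25 a year are already 30% of those eligible.

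**Conclusion.** The point holds for the complication trigger only. Its 90-day time point matches no scheduled complication assessment, and ascertainment of days 31 to 90 is incomplete at the interim for patients who have not reached Month 6.

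With about 9 evaluable patients per arm at best, a ratio above 1.5 says little in either direction. It appears in roughly a quarter to a third of studies with no true difference, and is absent in 38% to 55% when the risk is truly doubled. This rests on even accrual at the planned rate, no treatment delay, assumed control risks of 4.9% to 20%, the ratio taken at face value, and zero control events with any cryoablation event counted as a trigger.

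This should be corrected before the interim look. It does not undermine the trial's primary aim, which is recruitment.

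**What to change.** Reconcile the trigger's time point with the collection schedule in one of two ways, the choice being the sponsor's:

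- evaluate the trigger at a time at which complications are already collected; or
- keep 90 days and capture complications then, through the 3-month questionnaire contact or the telephone contact for which permission is already sought, and add that time to the outcome definition and Table 1.

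The first option affects how many patients count at the interim. By the same accrual arithmetic, about 6 per arm have reached Month 6, and 25 × 11/12 = 22.9, about 11 per arm, have reached 30 days.

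In either case, keep the 50% margin. State that the Data Monitoring Committee will receive the number with a complication and the number evaluable in each arm, and the risk difference with an exact confidence interval. The risk difference stays defined when the control arm has no event. Say that neither a trigger nor its absence is to be read from the ratio alone.

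The cost is a protocol wording change and a short interim table, plus either one more item at an existing contact or a different evaluation time for the rule.

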### Trial assessments, data collection and data items

Case report forms (CRFs) will have either paper or electronic format. The CRFs will not bear the participant’s name or other directly identifiable data. The participant’s trial identification number (ID) only will be used for identification. All study-related procedures will be carried out during routine clinical visits. To maximise completeness of data, participants will also be asked for permission for research personnel to contact them via telephone. Quality control will be applied at each stage of data handling to ensure that all data are reliable and have been processed correctly. Completed CRFs will be checked for completeness and accuracy by designated individuals, against the source data. When the original CRFs are in paper format, they will be used when entering information into the computer database. The database will be checked against the CRFs for accuracy. No investigation of the data will begin until an accurate database has been assured. The CRFs will not bear the participant’s name or other directly identifiable data. The participant’s trial identification number (ID) only will be used for identification.

If a participant chooses to discontinue study participation, they should continue the follow-up schedule defined in the protocol, provided they are willing. However, if the participant confirms they do not wish to participate in the scheduled follow-up data collection visits, then data that have already been collected should be kept and analysed according to the intention-to-treat principle for all participants who stop follow-up early. Participants who stop the trial follow-up early will not be replaced.

Baseline data items include the following:medical and surgical history, including previous diagnosis of RCC-related hereditary syndrome, comorbidities and calculation of age corrected Charlson comorbidity index and performance status,current medication,allergies,physical examination, focused on abdomen (as per clinician discretion),baseline blood results (full blood count, renal function),renal tumour characteristics (complexity scoring, location, unifocality),body mass index, height and weight,occupation,ethnicity,family history of RCC or diagnosis of RCC-related hereditary syndrome,referral centre and date of referral,quality of life questionnaire (EQ-5D-5L).

For patients who will not take part in the second stage of the study (intervention), subsequent assessments will be similar in frequency and content to post-intervention assessments (except for post-procedure assessment at 4 weeks).

The following data items will be assessed at time of intervention and immediately post-procedure:type of anaesthesia (general, sedation and local),operative complications,adverse events (AEs) during and post-procedure,routine blood tests post-procedure (as per clinician discretion),pain score post-procedure (daily),length of hospital stay.

The first post-procedure assessment happens face-to-face 4 weeks after surgery. The frequency of subsequent clinical assessments will be decided based on routine clinical follow-up. Subsequent assessments can be conducted face-to-face or via telephone, as per patient and clinicians’ discretion. In the majority of patients, this will happen every 6–12 months for 5 years. In the first post-procedure and each subsequent assessment, the following will usually be assessed:routine blood tests (as per clinician discretion),physical examination, focused on abdomen (as per clinician discretion),cross-sectional or ultrasound imaging (as per clinician discretion),complications,pain score,quality of life questionnaire (EQ-5D-5L).

In addition to standard of care diagnostic samples, biological samples obtained for research purposes will be obtained at each study visit in accordance with the consent form and patient information sheet. All participants will be asked to consent for the samples to be used for current and future ethically approved research. These will include blood, urine and tissue samples. Samples will be processed and stored indefinitely in pseudo-anonymised form centrally in accordance with all applicable legal and regulatory requirements, including the Human Tissue Act 2004 and any amendments thereafter.

After the end of the trial, participants will continue follow-up as per usual care.

### Statistical methods

This is a feasibility study; therefore, all analyses should be considered exploratory. Data will be analysed on an intention-to-treat basis.

### Adverse events

All AEs will be recorded in the hospital notes in the first instance. A record of all AEs, whether related or unrelated to the treatment will also be kept in the CRF and the AE Log. The AE Log will be sent to the Sponsor on request and every 2 months. If the Investigator suspects that the disease or condition has progressed faster due to the trial intervention, this will be reported to the Sponsor. Clinically significant abnormalities in the results of objective tests (eg, laboratory variables, CT) may also be recorded as AEs.

All serious AEs will be reported both to the Sponsor within 48 hours of the investigator becoming aware of the event and via email to the relevant REC. The Chief or Principal Investigator will respond to any serious AE queries raised by the Sponsor as soon as possible. Events will be followed up until resolution; any appropriate follow-up information will be clearly marked as such and reported to the Sponsor in a timely manner. Full reports should be completed and submitted to REC within 15 days of the event.

All deaths will be reported to the Sponsor irrespective of whether the death is related to disease progression, the intervention or an unrelated event.

### Data auditing

The investigators and site will permit trial-related monitoring, audits, REC review and regulatory inspection(s), providing direct access to source data and documents. Trial participants are informed of this during the informed consent discussion. Participants will consent to provide access to their medical notes.

### Patient and public involvement

An online survey was done in collaboration with the charity Kidney Cancer UK to ascertain broad acceptability of the study’s design and willingness of patients to be recruited into NEST (results described in ‘Introduction’). This online survey suggests strong support and need from the kidney cancer patient community for the broad concepts of the study.

Two patient representatives helped draft the study protocol, patient information sheets and consent forms. One patient representative is a co-author of the present paper, will represent patient views on the trial management committee and will have a central role in the design of the full trial and dissemination of study findings.

### Ethics and dissemination

Ethical approval has been granted (UK HRA REC 19/EM/0004). Protocol amendments will be promptly disseminated via post or email to the Sponsor, all research team, Trial Management Group members, Trial Steering Committee members and Data Monitoring Committees. They will also be recorded on the trial registration website (ISRCTN18156881, registered 04/03/2019).

The Chief Investigator is the data guarantor and holder. Study outputs will be presented at national and international conferences and published in peer-reviewed journals. Professional writers will not be involved in writing the main trial report. Patient representatives will be involved in output dissemination.

10.1136/bmjopen-2019-030965.supp2Supplementary data

10.1136/bmjopen-2019-030965.supp3Supplementary data

10.1136/bmjopen-2019-030965.supp4Supplementary data

10.1136/bmjopen-2019-030965.supp5Supplementary data
